#### Secondary objectives

These clinical outcomes will enable the project team to further refine the methodology to ensure optimal efficiency in terms of both delivering and assessing the treatment in a full-scale trial.

•Optimal stimulation target (OFC, SMA)

•Likely magnitude of effect of the intervention on OCD symptoms, to determine standard deviation of the outcome measure, to estimate sample size

•Duration of effect of stimulation, to space treatments efficiently

•Usefulness and limitations of specific neurocognitive tests to determine a definitive test battery

Additionally, qualitative data will be collected from participants to better understand their experience of taking part in a tDCS intervention, as well the impact on their overall quality of life.

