### Sample size calculation

Study sample size is evaluated with respect to the primary outcome (difference in the challenge Y-BOCS between tDCS and Sham), given that the aim is to estimate the likely effect size of a future trial. We assume that the sample will be representative of the population, and that the observed variance, and Y-BOCS scores in each condition will allow for estimation of a typical group comparison. Given that there are only 4 exposures of tDCS in each study condition, with 4 weeks between exposures, we assume no carry-over effects, which will be tested using a mixed model. Each tDCS target (OFC and SMA) will be considered independently against Sham. Published estimates of effect size vary widely [45]; thus, a conservative estimate of *d* = .3 is assumed. Following Cocks and Torgersen [51], assuming *α* = 0.05, 1 – *β* = 0.80, a sample size of 20 per group allows detection of a lower limit of *d*’ > 0.1 for an expected effect size *d*’ = 0.3. An additional 5 patients will allow for a 25% dropout.

It is estimated that approximately 25 patients will be recruited from a pool of 200 patients identified from screening, giving power to estimate the ascertainment ratio to within ± 6%. The proportion of missed treatment sessions is expected to be less than 20% from a total of 206 sessions, giving a precision within ± 6%. At the outset of the study, it is not possible to estimate the likely number of reported adverse events (safety), which is expected to be low, and cannot therefore estimate the likely precision of estimation.

Time-dependent changes in the Y-BOCS scores, and in the CANTAB test scores will be considered using standard paired comparisons (*t* test). A sample size of *N* = 20 allows for detection of an effect size *d*’ = .65 with power 1 – *β* = .78, and an effect size *d*’ = .77 with power 1 – *β* = .90. A time-dependent model will be evaluated (mixed model) to examine trends over time, but with limited power.

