##### Duration of effect

Change over time will be evaluated separately for the OFC and SMA targets using paired tests, identifying the time point (1, 2 and 4 h or 1, 7 and 14 days) at which the Y-BOCS returns to pre-stimulation levels. A mixed model may be evaluated where this may provide additional useful information about the trajectory of the Y-BOCS score over time (growth models).

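### Duration of effect is dated by paired tests with no margin, so at 20 patients a non-significant result can be taken for loss of effect

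*Protocol article*

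**What the plan says.** Duration is a named secondary objective in the protocol article: "Duration of effect of stimulation, to space treatments efficiently".

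The analysis is in the Duration of effect section. Each active target is examined on its own with paired tests, and the stated purpose is "identifying the time point (1, 2 and 4 h or 1, 7 and 14 days) at which the Y-BOCS returns to pre-stimulation levels". The section does not say how close to the pre-stimulation level counts as a return. It then adds that a mixed (growth) model may be fitted where it gives useful extra information on the trajectory.

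The Sample size calculation section says that time-dependent changes in the Y-BOCS will be compared by paired t tests. It states that the planned number of patients "allows for detection of an effect size *d*’ = .65 with power 1 – *β* = .78"; the second figure it gives is power .90 at d' = .77. On the longitudinal model the same section says: "A time-dependent model will be evaluated (mixed model) to examine trends over time, but with limited power". So the mixed model is optional in one section and firm in the other.

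**The concern.** A paired test can show that a score differs from its pre-stimulation value. Failing to show a difference does not show that the score has gone back. With paired tests as the only firm tool named in the duration section and no margin, the analyst has one way to name a time of return: the first listed time at which the test is not significant.

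In a small trial such a result may reflect decay or only sampling error. The error runs one way. Low power makes the effect look shorter than it is, and a larger trial with the same decay would report a longer duration. What is at stake is the treatment spacing carried into the definitive trial.

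**Working it through.** **Inputs from the protocol article.** Six listed times: 1, 2 and 4 h, and 1, 7 and 14 days (Duration of effect). Paired t test, N = 20, α = 0.05, d' = .65 and .77 (Sample size calculation). Sidedness is not stated; two-sided is used because it reproduces the protocol's power.

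**Assumptions, not in the protocol.** Change scores are normal with equal SD. Their correlation between any two times is .5 or .8. The true effect is the same at all six times, so it never fades.

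**Step 1: the protocol's own figures.** Power comes from the noncentral t distribution with 19 degrees of freedom, noncentrality d·√20 and critical value 2.093.

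- d = .65: noncentrality 2.907, power .787 (stated .78).
- d = .77: noncentrality 3.444, power .904 (stated .90).

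Both are reproduced; one-sided tests would give .876 and .953. The arithmetic in the protocol is sound.

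**Step 2: one test, other effects.** At d = .3, power is .247. The Background reports an active-arm change of 6.68 (SD 5.83) in an earlier trial, and 6.68 / 5.83 = 1.15. At that effect, power is .998.

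**Step 3: six tests, effect never fading.** Two limits bracket the chance of at least one non-significant time. If the tests always agreed, it would be 1 − power. If they were independent, it would be 1 − power⁶. At .65 the limits are 1 − .787 = .21 and 1 − .787⁶ = .76. At .77 they are .10 and .45. Simulation (40,000 trials per setting; repeat runs agree to about a point) gives the values between:

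| True change in SDs of the change score | One test non-significant | At least one of six non-significant (correlation .8 to .5) |
|---|---|---|
| .3 | 75% | 91–97% |
| .65 | 21% | 40–55% |
| .77 | 10% | 21–32% |
| 1.15 | 0.2% | under 1% |

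The tests may also fail to give a clear date. A non-significant time is followed by a significant one in about 30–48% of trials at .65 and 17–27% at .77.

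**Step 4: same decay, different N.** Assume a 14-day half-life from d = .65 and correlation .6. The true effect at 24 h is then still .65 × 0.5^(1/14) = .62. A first non-significant time falls within 24 h in about 46% of trials at N = 20 and in about 0% at N = 80. Starting from .77 the N = 20 figure is about 25%, and from 1.15 it is under 1%. Between N = 20 and N = 80 only the sample size changed.

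**Step 5: what estimation could offer.** The 95% CI half-width at N = 20 is 2.093 / √20 = 0.47 SD of the change score.

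**The case against.** **The rule is inferred.** The duration section never says that the first non-significant test marks the return, and an analysis plan that is not shown could add a criterion. That is fair, and the point is worded accordingly. But the section does name its method and what the method is to identify, and paired tests without a margin offer no other route to a date.

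**The planning effect is not the effect tested here.** A reader might put the protocol's d = .3 into these tests, find 25% power, and conclude that a lasting effect would usually be reported as gone, often at the first time. The document does not support that. The .3 is the expected difference between tDCS and sham. The duration tests concern change within one active condition, which also contains any placebo response and time trend and may be larger. For time-dependent changes the protocol quotes .65 and .77, and these are detectable effects, not predicted ones. The earlier trial's 1.15 would almost remove the problem, but it came from a longer course in treatment-resistant patients, so it is one end of a range.

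**A longitudinal model is planned.** A reader might infer from the duration section that the trajectory model is merely optional. The Sample size calculation section says it will be evaluated and admits limited power, and the Effect of tDCS section has scores estimated at all time points in all three conditions. What remains is that the two sections disagree on the model's status and that duration is tied to the paired tests.

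**Little hangs on it.** Duration is one of four listed secondary objectives and is not among the principal data under Progression to a full trial. This lowers the severity but does not make the method suitable for its purpose.

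**Conclusion.** The point holds at moderate severity. As written, the duration analysis has no means of showing a return to pre-stimulation levels. Its practical reading takes non-significance as loss of effect and errs towards too short a duration.

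The size depends on the unknown change within a condition. At the protocol's own paired-test effects, a permanent effect would show at least one non-significant time in roughly a fifth to just over a half of trials. It would be nearly all trials at .3 and almost none at about 1.15. These figures rest on 20 evaluable patients, two-sided 5% tests and an assumed correlation of .5 to .8 between times. The document does not support the claim that a lasting effect would usually be declared lost, nor that the decision to progress turns on this result.

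**What to change.** In the Duration of effect section:

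- Remove the dating of a return by paired tests, and state that a non-significant change is not evidence of return.
- Make the mixed model the stated duration analysis, so that this section agrees with the Sample size calculation section.
- Report, at each listed time, the estimated change from that course's pre-stimulation reading and the difference from sham, each with a 95% CI.
- Judge loss of effect against a pre-stated margin on the Y-BOCS version in use at that time. Table 1 has only the Challenge version at 1, 2 and 4 h. A fraction of the 24 h value would not serve: it cannot date an effect lost within hours, and it is unstable when the 24 h effect is near zero.
- Label the result descriptive.

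The cost is wording only; data collection is unchanged. The downside is wide intervals, with a half-width of about 0.47 SD of the change score at N = 20, and possibly no single date. That is an honest account of what 20 patients can show about duration.

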##### Evaluation of neurocognitive test

The effects of the tDCS target on neurocognitive function will be evaluated for each target and test separately, by documenting test scores at each time point (baseline, 3 h). Differences in the profile of effect will be evaluated on the test dimensions dependent on the target (SMA target: motor impulsivity; OFC target: cognitive flexibility, cooperation). Comparison will proceed using paired tests, and if study power permits, mixed models.

### Progression to a full trial

The decision whether to progress will be based on consideration of all findings, but principally on the following data:The acceptability of tDCS will be considered throughout the ascertainment ratio (target 10%), willingness of clinicians to recruit to the study, and the numbers of patients citing tDCS as the reason for refusal (< 20%).Feasibility of recruiting sufficient patients in a multicentre national study will be evaluated in relation to the population size in each of the study centres, and extrapolation to the number of centres required to achieve the required sample size for a full-scale trial.The study targets a lower limit for the effect size of tDCS > .1, giving confidence that the effect of tDCS is at least .3. The study will enable evaluation of the superiority of the two tDCS target sites (OFC or SMA, given limited power).Differences between the targets will be considered in the light of differences in the profile of the neurocognitive tests indicating that the changes are consistent with the hypothesised effects (SMA target: motor impulsivity; OFC target: cognitive flexibility, cooperation).

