
### Recruitment

Recruitment will primarily take place at 2 outpatient centres: Rosanne House (Welwyn Garden City, Hertfordshire Partnership University NHS Foundation Trust) and University Department of Psychiatry, College Keep, Southampton. Camden and Islington NHS Trust will also act as a Participant Identification Centre (PIC). It is expected that 200 patients will be screened to allow for recruitment of 25 patients (Fig. 1). This will provide a robust estimate of the ascertainment ratio for recruitment to the study (limits within ± 10%).

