#### For patients identified from primary health care services (e.g. IAPTs), charity/support networks, adverts/promotional material

OCD charity and support networks have given their support to the protocol and will advertise the study to their membership. Any patients who express an interest in the study will be sent information about the trial which will give a number to call to discuss further. Potential participants who respond to an advert or promotional material about the study will be sent information about the trial by one from the research team. Adverts/promotional material may be placed in primary health care services, health clinics attracting high levels of OCD patients, local newspapers, appropriate websites and relevant noticeboards. Research team members may also advertise the study through other media channels (e.g. local radio, patient support groups). Patients who express interest will be contacted by the researchers to discuss the study. If agreeable, a consent form and prepaid envelope will be sent. A clinician will be available to call the patient to discuss any queries that they may have. The patient will be asked to sign the consent form and post it to the research site, once received the clinician will arrange a convenient time to conduct the screening phone call. At the beginning of the screening phone call, the clinician will talk through the consent form with the patient to ensure that they have fully understood what they are consenting to, then countersign the signed consent form that had been sent by the patient.

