#### For patients identified from the Trust databases

Patients who have a probable diagnosis of OCD on Trust databases will be identified by the clinical studies officers, research nurses, research assistants or research doctors. The treating clinician will be contacted and the suitability of the patient for the study discussed. If the treating clinician believes it is appropriate, the patient will then be referred to the study team for potential recruitment. Information about the trial will also be disseminated to clinicians. If they have suitable patients, they will refer them to the study team. The patient, if agreeable, will then be contacted by a member of the research team to see if they are interested in participating in the study. If interested, the patient will be sent an information sheet, consent form and prepaid envelope. A clinician will be available to call the patient to discuss any queries that they may have. The patient will be asked to sign the consent form and post it to the research site; once received, the clinician will arrange a convenient time to conduct the screening phone call. At the beginning of the screening phone call, the clinician will talk through the consent form with the patient to ensure that they have fully understood what they are consenting to, then countersign the signed consent form that had been sent by the patient.

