### Screening

Patients will consent to be screened for the study. A member of the research team will assess eligibility according to the eligibility criteria and take a brief medical history. The results of all screening will be recorded both in the patients’ medical notes and on the study case report form (CRF). Eligibility criteria will be confirmed by the clinician who will be delivering the intervention.

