#### Willingness of clinicians to recruit participants

The numbers of patients identified, screened and randomised will be evaluated by study site. Differences between sites will be considered and potential differences, such as the willingness of clinical staff to refer patients, considered.

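### The progression criterion reads acceptability of tDCS from recruited/screened, which mixes ineligibility with refusal, and its companion limit on tDCS-related refusal has no stated base

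*Protocol article*

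**What the plan says.** In the protocol article, Progression to a full trial lists the data on which the decision will mainly rest. The first item reads "The acceptability of tDCS will be considered throughout the ascertainment ratio (target 10"%), and adds the willingness of clinicians to recruit and "the numbers of patients citing tDCS as the reason for refusal (< 20"%).

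The ratio's two counts are given elsewhere. Recruitment says "It is expected that 200 patients will be screened to allow for recruitment of 25 patients", and Sample size calculation says "approximately 25 patients will be recruited from a pool of 200 patients identified from screening, giving power to estimate the ascertainment ratio to within ± 6"%. Screening is the step at which eligibility is decided: "A member of the research team will assess eligibility according to the eligibility criteria and take a brief medical history".

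For clinicians, the section on their willingness to recruit says "The numbers of patients identified, screened and randomised will be evaluated by study site". Those counts draw on different routes. On the Trust database route, "The treating clinician will be contacted and the suitability of the patient for the study discussed". On the charity and advert route, "OCD charity and support networks have given their support to the protocol and will advertise the study to their membership", and people who respond deal directly with the research team.

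**The concern.** Acceptability of the intervention and willingness of clinicians to recruit are both listed under the primary objective, and both appear among the main progression data. A measure of acceptability should move when patients' readiness to accept tDCS moves, and should otherwise stay still. Recruited over screened does not behave like this. With a long list of exclusions applied at screening, it also moves with the share of screened patients who qualify.

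The limit on tDCS-related refusal is the more direct measure. However, it attaches a percentage to a number of patients without saying a percentage of whom, so the base could be settled after the data are seen.

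For clinicians, site totals that include people who answered an advert do not show how ready treating clinicians were to refer.

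**Working it through.** **Inputs.** 25 recruited, 200 screened, 10% target and 20% limit, all from the protocol article. Let E be the number eligible among the 200 and R the number randomised. E is not given, so a range is shown as an assumption. Eligible patients who are not randomised are treated as declining.

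**1. The plan's own figure.** 25/200 = 12.5%. The 95% half-width is 1.96 × √(0.125 × 0.875/200) = 4.6 percentage points. The exact (Clopper-Pearson) interval is 8.3% to 17.9%, with a largest half-width of 5.4 points. The stated ± 6% therefore holds as an upper bound. The precision is not the problem; the question is what the ratio measures.

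**2. What the ratio measures.** R/200 = (E/200) × (R/E), that is, eligible fraction × uptake.

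| Eligible E | Randomised R | Ratio R/200 | Uptake R/E | Decline (E − R)/E |
|---|---|---|---|---|
| 25 | 25 | 12.5% (target met) | 100% | 0% |
| 50 | 25 | 12.5% (met) | 50% | 50% |
| 60 | 25 | 12.5% (met) | 41.7% | 58.3% |
| 100 | 25 | 12.5% (met) | 25% | 75% |
| 18 | 18 | 9% (missed) | 100% | 0% |

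With 25 randomised, a majority of eligible patients decline once E exceeds 50, a quarter of those screened. At exactly the 10% target (R = 20), this happens once E exceeds 40, a fifth of those screened.

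**3. The base of the under-20% limit.** Two illustrative cases, each with 25 randomised:

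| Case | Of 200 screened | Of eligible | Of refusers |
|---|---|---|---|
| 35 eligible refusers, all citing tDCS (E = 60) | 35/200 = 17.5% (met) | 35/60 = 58.3% (not met) | 35/35 = 100% (not met) |
| 10 eligible refusers, 2 citing tDCS (E = 35) | 2/200 = 1% (met) | 2/35 = 5.7% (met) | 2/10 = 20% (not met) |

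In each case the choice of base alone changes the reading.

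**4. Where refusal can occur.** On every recruitment route patients receive trial information and return a consent form before the screening call, so some can decline before their eligibility is known. Let D be the number of such early decliners, and d ≤ D the number of them who would have been eligible. True uptake among eligible patients is R/(E + d), which lies between R/(E + D) and R/E. Confirmed-eligible uptake R/E alone therefore flatters acceptability whenever d > 0, and counting all early decliners gives the lower end.

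**5. Clinician willingness.** No arithmetic applies. On the database route a clinician's decision stands between identification and referral. On the advert and charity route no treating clinician has to refer. Counts by site add the two, so a site with active advertising and reluctant clinicians can show the same totals as a site with willing clinicians and little advertising.

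**The case against.** The strongest reply is that the ratio does not stand alone. The same item contains a direct limit on tDCS-related refusal, and majority refusal because of tDCS breaches it on two of the three possible bases. The decision also draws on everything found. Missed and shortened sessions are summarised with reasons, patient flow and reasons for refusal are logged, and patients, those who leave early and research staff can be interviewed. The 10% is called a target, not a stopping rule.

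Much of this stands. A reader might infer that the plan will declare tDCS acceptable while most eligible patients refuse it. The documents do not support that. It requires the 20% limit to be taken over all screened patients, an eligible fraction that is nowhere given, and a mechanical decision rule that the protocol does not contain. On that one reading, up to 39 tDCS refusals pass (39/200 = 19.5%). The resulting 39/(39 + 25) = 61% is a share of acceptors plus tDCS refusers only; other eligible refusers would lower it as a share of all eligible patients.

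A reader might also infer that a numeric criterion on clinicians can be wrongly met. None exists. The section sets no threshold and treats willingness as one possible explanation of differences between sites, and the drop from identified to screened carries some information.

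An article may leave the base of a percentage to the full protocol. That softens the second part but not the first: the article itself assigns the recruited/screened ratio to acceptability.

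**Conclusion.** The point holds as a weakness in what is measured. The ascertainment ratio suits recruitment feasibility but cannot be read as acceptability: 12.5% fits any uptake from 100% (25 eligible) to 25% (100 eligible), and beyond if more are eligible, while full acceptance among 18 eligible patients misses the target. The limit that could correct this has no base, and the base can reverse its reading (17.5%, 58% or 100% from the same data). For clinician willingness, pooled site counts cannot isolate the quantity of interest.

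All splits into eligible, accepting and refusing patients are assumptions. They show what the criterion permits, not what the trial will find.

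**What to change.** In Progression to a full trial:

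- Use the 10% ascertainment ratio for recruitment feasibility only.
- Judge acceptability by uptake among patients given the trial information and not found ineligible: randomised / (randomised + eligible patients who decline after screening + patients who decline before it).
- Apply the under-20% limit on tDCS-related refusal to that same base.
- Report uptake among confirmed-eligible patients beside it, so that the two figures bracket true uptake.

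In the section on clinicians' willingness to recruit, report clinician-routed patients by site as referred / discussed with the treating clinician, separately from people who came through an advert or charity.

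The cost is small. A screening log, a CRF record of screening results and a log of patient flow are already planned. Their fields are not shown, so the team should check that they capture route, eligibility, and the stage and reason for declining. The price is smaller denominators with wider intervals, and eligibility that stays unknown for some early decliners.

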## Method/design

### Aim

#### Primary objective

The main aim of this feasibility trial will be to inform the development of a subsequent definitive tDCS full-scale trial. This feasibility trial will collect information about recruitment, study conduct, tDCS delivery, and assessment methods to inform future trial design.

The objectives of this feasibility trial will be to assess:

•Acceptability and safety of the intervention

•Feasibility of recruitment

•Adherence and tolerability of tDCS and study assessments

•Willingness of clinicians to recruit participants

•Practicality of applying tDCS in the clinical setting

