#### Acceptability, tolerability and safety

Treatment logs will be maintained, and the number of completed, shortened and missed sessions will be summarised by treatment condition. Reasons for refusal to complete or missing a treatment session will be recorded and tabulated. Comparison between treatment conditions will be evaluated using a McNemar test.Incidents related to safety and tolerability will be logged during the exposure to tDCS and in the following weeks. The nature of the adverse events will be documented, classified (as outlined in the “Measures” section) and listed. The number of scope of the events in each of the study conditions will be compared using a McNemar test.

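### The principal progression criteria contain no adherence, tolerability or safety item, although these are objectives under the primary aim and the data are already collected by condition

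*Protocol article*

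**What the plan says.** All references are to the protocol article.

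- **Progression to a full trial.** "The decision whether to progress will be based on consideration of all findings, but principally on the following data". The list then gives acceptability, which is assessed as follows: "The acceptability of tDCS will be considered throughout the ascertainment ratio (target 10%), willingness of clinicians to recruit to the study", together with "the numbers of patients citing tDCS as the reason for refusal (< 20"%). After that come the feasibility of multicentre recruitment, an effect-size criterion ("The study targets a lower limit for the effect size of tDCS > .1"), the comparison of the OFC and SMA targets, and the neurocognitive profile.
- **Primary objective.** The feasibility objectives include acceptability and safety of the intervention and "Adherence and tolerability of tDCS and study assessments". Optimal target, magnitude of effect and choice of neurocognitive tests are under Secondary objectives.
- **Acceptability, tolerability and safety (statistical analysis).** Here "the number of completed, shortened and missed sessions will be summarised by treatment condition". The section also has staff log why a patient refused to finish a session or missed one, and it compares adverse events between conditions.
- **Adherence to tDCS and study assessments.** There are 12 sessions per patient, and the proportion completed is to be estimated.
- **Sample size calculation.** "The proportion of missed treatment sessions is expected to be less than 20"%, from a total of 206 sessions, with a precision within ±6%.

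**The concern.** The principal list does not follow the protocol's own order of importance. It includes two matters that the protocol calls secondary (effect size and neurocognitive profile). It leaves out adherence, tolerability and safety, which the protocol places under its primary aim.

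The word acceptability also carries two meanings. In the analysis section it heads completed, shortened and missed sessions and adverse events. In the progression section it means the ascertainment ratio, clinician willingness and refusals. The meaning based on exposure to the stimulation does not reach the decision list. The one numeric expectation about adherence, under 20% missed, is not linked to any decision.

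At stake is what the study can conclude about the regimen. A course or target with substantial non-completion could go forward without any principal item registering it. The choice between OFC and SMA is affected too. The protocol concedes limited power to separate them on effect, and that is the situation in which completion by target would be most useful.

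**Working it through.** **1. The plan's own adherence figure.** Inputs from Sample size calculation: p = 0.20, n = 206. The 95% half-width is 1.96 × √(p(1−p)/n) = 1.96 × √(0.16/206) = 0.055. The stated ±6% is reproduced as a bound.

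**2. The denominator.** At 12 sessions per patient, 20 patients give 240 sessions and 25 give 300. The stated 206 matches neither, and 206/12 = 17.2 is not a whole number of patients. The same formula gives ±5.1% on 240 and ±4.5% on 300.

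**3. Which principal items respond to non-completion?**

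| Progression item | Responds to missed or shortened stimulations? |
|---|---|
| Ascertainment ratio, target 10% | No. It is fixed at randomisation: 25/200 = 12.5% whether 25, 20 or 10 patients complete |
| Clinicians' willingness to recruit | Not directly; no number attached |
| Refusals citing tDCS, under 20% | No, if refusal means declining to take part. Partly, if it also means declining to complete sessions. Neither stage nor denominator is stated |
| Multicentre recruitment feasibility | No |
| Lower limit of effect size above 0.1 | Indirectly, through precision (step 5) |
| OFC/SMA comparison, neurocognitive profile | Not as a criterion |

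**4. Illustration.** Take 25 of 200 recruited (12.5%), under 20% of refusals citing tDCS, and 40% of 300 planned stimulations missed (0.40 × 300 = 120). Reading refusal as refusal to take part, both numeric feasibility criteria are met at twice the plan's 20% expectation.

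**5. Would the effect-size criterion catch this?** The type of lower limit is not stated. Assume a one-sided 80% limit with standard error 1/√n. For d = 0.3 and n = 20 this gives 0.3 − 0.842/√20 = 0.112, consistent with the stated target of above 0.1. The observed d needed is then 0.1 + 0.842/√n:

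- n = 20: 0.29
- n = 12: 0.34
- n = 10: 0.37

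Poor completion raises the bar if it reduces the number of patients analysed, but does not by itself fail the criterion.

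**6. Precision if adherence were added.** At p = 0.20:

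- Per target, 25 × 4 = 100 stimulations: 1.96 × √(0.16/100) = ±7.8% if independent. With an assumed within-patient correlation of 0.3, the design effect is 1 + 3 × 0.3 = 1.9, and ±7.8% × √1.9 = ±10.8%.
- Over all conditions, with an assumed correlation of 0.1 to 0.5, the design effect 1 + 11 × ICC is 2.1 to 6.5. The half-width is ±6.6% to ±11.5% on 300 sessions and ±7.3% to ±12.9% on 240.

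The documents give no within-patient correlation; these values are assumptions that show the range.

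**The case against.** The strongest reply is that the progression section describes an overall assessment and not an algorithm. Since all findings are to be considered, a reader who inferred that adherence and tolerability count for nothing would be wrong: they lack principal and quantified weight, but they are not excluded. That reply stands, and it limits the point. It does not explain why secondary outcomes are named as principal while objectives under the primary aim are not.

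Three further inferences are tempting and not supported.

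- **That a poorly completed regimen would meet every listed criterion.** It could. The effect-size criterion becomes harder to meet with fewer patients analysed (step 5), and the illustration covers the numeric feasibility criteria only.
- **That the refusal criterion counts only refusals before exposure.** This is the natural reading beside the ascertainment ratio, and Feasibility of recruitment speaks of refusal to take part. But the analysis section also uses the word for refusing to complete a session, and the progression section does not say which applies.
- **That the effect size is estimated only in patients who stay.** End of trial says that patients who stop tDCS will be asked to continue assessments, and nothing restricts the analysis to completers. Some patients are withdrawn under the Withdrawal criteria, but the size of any resulting selection cannot be established from the document.

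It is also fair that tolerability is not unattended. It is recorded in the CRF, adverse events are compared by condition, and safety concerns go to the Trial Steering Committee. These arrangements make an unnoticed problem less likely, but they do not make it a principal ground for the decision.

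**Conclusion.** The point holds as a gap in the principal criteria. No listed item covers adherence, tolerability or safety, and the under-20% missed-session expectation has no role in the decision. The numeric feasibility criteria could be met with 40% of stimulations missed, leaving only unquantified consideration of all findings to register it.

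This rests on reading refusal as refusal to take part. If refusal to complete sessions is also meant, the second numeric criterion would capture part of the problem, though only where patients cite tDCS.

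The gap should be closed before the progression decision. It does not undermine the study's data, which are already planned for collection. A strict 20% threshold for each target is not supportable: the plan's figure is an expectation, pooled over conditions and for missed sessions only. At about 100 stimulations per target, true rates near 20% would pass or fail largely by chance.

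**What to change.** In Progression to a full trial:

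1. Add to the principal list the proportion of planned stimulations missed, overall and by condition beside sham. Use the plan's own expectation of under 20% as a guide value for the overall figure, not as a pass/fail threshold per target.
2. Report shortened sessions, severe adverse-effect ratings (grade 4 on the questionnaire) and discontinuations for tolerability by target, and state that they inform the OFC/SMA choice.
3. Say whether refusal means refusal to take part or refusal to complete sessions, and give the denominator of the 20%.

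In Sample size calculation, reconcile 206 sessions with 12 per patient (240 for 20 patients, 300 for 25) and restate the precision, preferably allowing for repeated sessions within a patient.

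The cost is a few sentences and no new data. The downside is one more criterion that the study could miss, measured with modest precision (step 6), which is why a guide value with its interval is preferable to a cut-off.
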